### Training of Health Care Staff

A transition workshop will be delivered to a group of health care staff about preparing young people moving to adult services based on predetermined themes during the staff advisory group meetings (transition management, plans in action, coordination with receiving services, joint working, continuity of care, structural problems, infrastructural weaknesses, a structured health transition plan based on individualized needs, education in line with CPA reviews). This workshop will train health care staff to deliver the developing intervention to the young people who have agreed to participate in the study. Those delivering care as usual will not receive training. Health care staff will receive training 3 months pretransition in the form of two 45-minute workshops. The training will be standardized to increase intervention fidelity.

### Trial Conditions

#### Condition 1: T0 Baseline Pretransition (6-12 Months Before 18th Birthday)

As discussed with the advisory groups in the first stage of the coproduction/development phase, this intervention will include 4 modules delivered over 8 series of 2-day workshops. When the intervention is finalized, a manual will be developed including the goals and objectives of each workshop, skills developed, behavior expectations and management, themes that need to be covered, required materials for the sessions, and strategies for young people with neurodevelopmental needs. The content of the sessions will be the same across different groups of patients although adjustments will be applied to the intervention models based on each group’s mental health and developmental needs identified during the piloting phase with the lead sites (Ardenleigh and St Andrews). These adjustments will be discussed with the steering group to ensure that the intervention fidelity is not threatened. Additionally, monitoring procedures with the help of the research team across the study will enhance intervention fidelity. For example, young people with neurodevelopmental needs may need additional help in terms of mental health literacy and understanding the purpose of their prospective transition. The workshops will be delivered across 4 days, and there will be 4 sessions targeting different domains of transition. Staff members who attended the transition training will deliver these workshops as they are key attachment figures to the young people. Each workshop will take between 30-40 minutes. Key workers from the advisory groups suggested that the intervention should be informed by attachment-based therapy, CBT, SST, and psychoeducational elements, which target self-efficacy and management of mental health problems.

#### Condition 2: T0 Baseline Pretransition (Young People and Parents/Carers)

The same series of workshops will be delivered with involved parents/carers to examine whether parental involvement in the process yields different outcomes.

#### Condition 3: T0 Baseline Pretransition (TAU)

This group of young people will receive TAU (standard transition care through the CPA) depending on the service, which may or may not involve transition preparation.

#### Conditions 1-3: T1 (6-12 Months Posttransition)

Young people and parents/carers (condition 2) who received an intervention and those who received care as usual (condition 3) will be visited and interviewed at the receiving placement 6-12 months postdischarge. Outcome measures will be completed.

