#### Conditions 1-3: T2 (18-24 Months: Endpoint)

Young people and parents/carers (condition 2) who received the interventions and those who received care (condition 3) as usual will be followed up depending on an old or new placement and will be interviewed about continuity of care, mental health, overall well-being, education, employment, and relapse. Outcome measures will be completed.

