### Allocation Strategy

The adolescent secure service is the unit of randomization and will be randomly selected until 6 sites are recruited. Sites were eligible if they provided low or medium secure care, or they were classified as PICUs. Six adolescent secure hospitals will be randomly allocated into 1 of 3 arms in a 1:1:1 ratio, stratified by area (south versus north) and type (medium versus low versus PICUs) first. Then participants at each site will be allocated to the same treatment. A total of 4 secure units will be allocated to the intervention arms and 2 units allocated to the control arm. Allocation will be performed (computer-generated allocation) by an independent member of the team who will be blind to the identity of the unit. Considering the nature of the intervention, young people and health care staff will not be blinded. The statistician and all team members collecting follow-up data, apart from the principal researcher and fieldworkers, will remain blind to the allocation of the units to trial arms.

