### Progression Criteria and Feasibility Outcomes

A traffic light approach (stop-amend-go/red-amber-green) will be used and discussed a priori with PPI, advisory and local collaborators/key contacts, and research mentors about the following criteria:

Recruitment: at least 80% of targetIntervention fidelity: at least 80% of intervention workshops meet the fidelity criteriaIntervention acceptability: at least 80% of staff can be trained and deliver the intervention (barriers and facilitators to intervention design)Follow-up numbers: at least 70% at T1 and 60% at T2Acceptability of assessment tools: at least 70% at T1 and 60% at T2

The outputs are as follows:

Design a multicenter intervention for young people in transition;Design training manuals/toolkit for the health care staff involved in transition;Reflect on good practices across adolescent secure hospitals for transition to adult services and the community and management;Promote co-design and coproduction of evidence-based research.

The impact is as follows:

Design of the future cRCT will promote effectiveness and cost-effectiveness;Assess barriers and facilitators to providing the proposed intervention;Help services to reflect on quality of care and performance pre- and postdischarge;Enable young people to voice their experiences and be dynamically involved in their care.

Figure 3 presents the outcomes for the full-scale trial.

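### T1 and T2 follow-up is worded by what participants received, not by the arm their site was allocated to, so young people who never start the workshops may be left out in the intervention arms only

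*Protocol article*

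**What the plan says.** Under Allocation Strategy in the protocol article, the secure service is the unit of randomization: "Then participants at each site will be allocated to the same treatment". Arm membership therefore follows from the site, whatever an individual goes on to attend.

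The two paragraphs under Trial Conditions that say who is followed use a different rule. At T1: "Young people and parents/carers (condition 2) who received an intervention and those who received care as usual (condition 3) will be visited and interviewed". At T2: "Young people and parents/carers (condition 2) who received the interventions and those who received care (condition 3) as usual will be followed up". The article does not say whether one workshop or all four count as receipt.

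The usual-care arm is described under Condition 3 as standard care that differs by service, "which may or may not involve transition preparation".

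The third primary objective, under Aims and Objectives, lists adherence and follow-up as separate things to be tested. Progression Criteria and Feasibility Outcomes sets the follow-up target at "at least 70% at T1 and 60% at T2", with no denominator.

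**The concern.** A follow-up rule based on receipt can act on only one side of this comparison. A participant can miss the workshops. A participant can hardly miss usual care when usual care may consist of nothing specific to transition. If fieldworkers apply the T1 and T2 sentences as written, young people in conditions 1 and 2 who consent and complete baseline but never start may not be contacted again, while everyone in condition 3 is.

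Never-starters are plausible here. The Abstract spreads the workshops over 6 months, and the inclusion criteria admit people aged 17 or over who are already eligible to move on, so some may leave before delivery begins.

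Two things are at stake:

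- **Outcome data.** The Quantitative Analysis section takes the TROM difference, the between- and within-cluster variances and the ICC forward to the definitive trial. Those inputs could come from a selected group in four sites and an unselected group in two.
- **Feasibility result.** If follow-up depends on having started, the trial cannot show whether non-adherent young people can be retained, and two items that the third objective separates become one.

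**Working it through.** **1. The passages side by side**

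| Section | Rule stated | Basis |
|---|---|---|
| Allocation Strategy | All participants at a site share one arm | Allocation |
| Conditions 1-3: T1 | "who received an intervention and those who received care as usual (condition 3) will be visited and interviewed at the receiving placement" | Receipt |
| Conditions 1-3: T2 | "who received the interventions and those who received care (condition 3) as usual will be followed up" | Receipt |
| Feasibility Trial Design | Data collected at T0, T1 and T2 | Does not say from whom |
| Recruitment and Support | Retention plan and vouchers | No attendance condition |

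No section commits to following everyone allocated. None excludes never-starters expressly either.

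**2. The article's own figure.** The only computed figure is the precision for an 80% rate with n = 50: 1.96 × √(0.80 × 0.20 / 50) = 0.1109, or ±11 points. It reproduces, but it has no bearing on this point.

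**3. Illustration of the literal reading.** Inputs from the article: 50 young people; 4 of 6 sites in the intervention arms. With equal site sizes (my assumption), that is 50 × 4/6 = 33.3 intervention and 16.7 usual care. Two further quantities are assumptions, since the article gives neither: *s*, the share of intervention participants who never start, and *l*, other loss, taken as equal in all arms.

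- Followed, intervention arms: (1 − s)(1 − l). Followed, usual care: 1 − l. Gap between them: s(1 − l).
- Followed, as a share of all 50: (1 − l)(1 − 2s/3).
- Followed, as a share of those who received something: 1 − l.

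With l = 20%:

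| s | Intervention | Usual care | Gap (points) | Share of all 50 | Share of receivers |
|---|---|---|---|---|---|
| 10% | 72% | 80% | 8 | 75% | 80% |
| 20% | 64% | 80% | 16 | 69% | 80% |
| 30% | 56% | 80% | 24 | 64% | 80% |
| 40% | 48% | 80% | 32 | 59% | 80% |

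At s = 20%, the number followed is 33.3 × 0.64 + 16.7 × 0.80 = 34.7. That is 34.7/50 = 69%, or 34.7/43.3 = 80%. The same people fall just short of the 70% T1 target or pass it comfortably, depending on a denominator that the article does not state. If everyone were followed as allocated and never-starters were lost at the same rate *l*, all arms would stand at 80%.

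With no other loss and 50 as denominator, *s* would have to exceed 0.30/(2/3) = 45% before the 70% target was missed, and 0.40/(2/3) = 60% before the 60% target was missed.

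**4. What this cannot show.** The effect on the criteria changes direction with the denominator, and nothing in the article fixes *s*. The figures show that the wording can matter. They do not show by how much, or which way outcomes would move.

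**The case against.** The wording may simply be shorthand for the arms. Both paragraphs sit under headings that cover conditions 1 to 3, the sentences carry condition labels, and no section withdraws anyone for missing workshops. Listing adherence and follow-up as separate objectives also fits poorly with an intention to drop non-adherers. All of this stands as a reason not to claim a deliberate exclusion.

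At T1, the receipt clause governs visits and interviews, and completion of outcome measures is a separate sentence without a condition. This stands in part: that sentence names no other group, and the T2 clause governs follow-up as a whole.

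Three stronger readings are tempting, and the document does not support them:

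- A reader might infer that people who stop part-way are also lost. On ordinary reading, someone who attended one workshop has received an intervention, so the concern is about never-starters.
- A reader might infer that the bias favours the intervention. The article gives nothing on how never-starters would differ in outcome, so the direction is not established.
- A reader might infer that the follow-up criteria would be met on a reduced denominator. The article states no denominator, and the Sample Size section ties its dropout estimate to the full 50. On 50, leaving people out makes the target harder to meet.

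Finally, a condensed article may leave denominators and rules for stopping treatment to the full protocol. That is so, and their absence is not the point here. The receipt rule is stated, twice.

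**Conclusion.** The concern holds as a matter of wording that should be corrected. The T1 and T2 paragraphs describe the follow-up population by receipt although allocation is by site. Taken literally, they can leave out only young people in the two intervention arms, chiefly those who never start. That could select the intervention-arm data passed to the definitive trial, and it would confound adherence with follow-up.

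Its size is not derivable. Under the assumptions in the working (equal site sizes, 20% other loss in every arm, 10% to 40% never starting), the gap in follow-up between usual care and intervention would be 8 to 32 points. The article gives no non-receipt rate with which to choose within that range. If the authors already intend to follow everyone, the harm is only that sites could read the text otherwise.

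**What to change.** In the T1 and T2 paragraphs, replace the phrases about having received the intervention or usual care with: all consented participants at sites allocated to conditions 1, 2 and 3, regardless of workshop attendance, unless they withdraw consent for data collection. Under Progression Criteria and Feasibility Outcomes, calculate the T1 and T2 follow-up percentages on all of these participants.

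The cost is a change of wording in three places, a few extra follow-up contacts and possibly a slightly lower reported follow-up percentage.

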#### Conditions 1-3: T2 (18-24 Months: Endpoint)

Young people and parents/carers (condition 2) who received the interventions and those who received care (condition 3) as usual will be followed up depending on an old or new placement and will be interviewed about continuity of care, mental health, overall well-being, education, employment, and relapse. Outcome measures will be completed.

### Allocation Strategy

The adolescent secure service is the unit of randomization and will be randomly selected until 6 sites are recruited. Sites were eligible if they provided low or medium secure care, or they were classified as PICUs. Six adolescent secure hospitals will be randomly allocated into 1 of 3 arms in a 1:1:1 ratio, stratified by area (south versus north) and type (medium versus low versus PICUs) first. Then participants at each site will be allocated to the same treatment. A total of 4 secure units will be allocated to the intervention arms and 2 units allocated to the control arm. Allocation will be performed (computer-generated allocation) by an independent member of the team who will be blind to the identity of the unit. Considering the nature of the intervention, young people and health care staff will not be blinded. The statistician and all team members collecting follow-up data, apart from the principal researcher and fieldworkers, will remain blind to the allocation of the units to trial arms.

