**Objective:**

This paper presents the protocol for a study that aims to test a feasibility cluster randomized controlled trial for young people transitioning from adolescent secure services to adult-oriented settings. The overarching aim of the MOVING FORWARD study is to provide a preliminary estimate of the effectiveness and cost-effectiveness of a new transition intervention model and to inform a future full-scale cluster randomized controlled trial.

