### Feasibility Trial Design

This study is a mixed methods, multicenter, 3-arm, feasibility cRCT with a parallel design comparing the MOVING FORWARD intervention against standard transition preparation (usual care: Care Programme Approach [CPA] discharge and individual meetings with the responsible clinician) conducted at 6 adolescent secure sites, of which 4 units will receive the intervention and 2 will serve as controls. Young people across these adolescent secure services present with similar mental health and neurodevelopmental needs and complex trauma history. In this specific study, we will focus on those with emerging borderline personality disorder, psychosis, autism, learning disabilities, and conduct disorder. Data will be collected at 3 time points: baseline (time 0; T0), 6-12 months postintervention (time 1; T1), and 18-24 months postbaseline (time 2; T2). A cRCT will minimize the risk of contamination, which is high in the proposed study as elements from the intervention could be used for standard transition preparation.

A feasibility study will measure the acceptability of conducting a future, fully powered trial across different pools of young people in secure care and different settings across adolescent secure hospitals. This study will test how the future trial will look like, as well as the main research question and primary outcomes. Outcome measures and one-to-one semistructured interviews with young people, parents/carers, and health care staff will be conducted to explore the experiences of young people receiving the intervention and those who received treatment as usual (TAU). The practicality and integration of the intervention within the current system of care and use of resources will be explored with the participants. A total of 30 interviews will be sought to understand the mechanisms of impact.

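### The principal researcher and fieldworkers collect follow-up data but are exempt from blinding, and no role that administers the T1 and T2 outcome measures is identified as blind

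*Protocol article*

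**What the plan says.** On blinding, the Allocation Strategy section of the protocol article makes two statements. The first is "Considering the nature of the intervention, young people and health care staff will not be blinded". The second is that the statistician and "all team members collecting follow-up data, apart from the principal researcher and fieldworkers, will remain blind to the allocation" of units to arms. Allocation is by unit: "Then participants at each site will be allocated to the same treatment".

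On follow-up, the T1 section says that young people and, in condition 2, parents/carers "will be visited and interviewed at the receiving placement 6-12 months postdischarge. Outcome measures will be completed". The T2 section says that they "will be interviewed about continuity of care, mental health, overall well-being, education, employment, and relapse", and that the measures are completed then too. Neither section says which role makes the contact. The Feasibility Trial Design section adds one-to-one interviews about experience of the intervention or of usual care, with a total of 30 sought across young people, parents/carers and staff.

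On use of the outcomes, the abstract's Objective is to "provide a preliminary estimate of the effectiveness and cost-effectiveness of a new transition intervention model". The Quantitative Analysis section bases the size of the definitive trial on a between-arm difference estimated with the TROM.

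**The concern.** The blinding sentence offers some protection to outcome collection but withholds it from two roles that the same sentence treats as collectors. If either role administers the functioning, adjustment or quality-of-life questionnaires, this is done by someone who knows the arm. A collector who starts out blind could also learn the arm if an interview about the intervention comes before the questionnaires at the same contact.

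Help, prompting or clarification from someone who knows the arm can move scores in the direction that person expects. Any such shift would enter the preliminary effect estimate and the difference used to plan the next trial. Testing trial procedures and assessment tools is itself a primary objective here. If blind collection is not put into operation, the study will not show whether it is workable in the definitive trial.

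**Working it through.** No arithmetic applies to the main point. It rests on setting the article's statements side by side.

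1. **Who collects follow-up data?** The exception in Allocation Strategy is taken out of the group of team members collecting follow-up data. The principal researcher and fieldworkers therefore belong to that group. No other follow-up collecting role is named.

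2. **Who among them is blind?** Neither named collecting role is. The only named role that stays blind is the statistician, who is not described as collecting outcomes. The sentence implies that further, unnamed collectors are blind, but does not say what they administer.

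3. **When are the measures taken?** Both the T1 and the T2 sections pair an interview with the measures. The T1 contact is a visit to the receiving placement.

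4. **Could the contact itself reveal the arm?** It could, by several routes:
   - Some interviews explore experience of the intervention or of usual care (Feasibility Trial Design).
   - A whole site shares one arm, so the originating unit discloses the arm to anyone who knows that unit's allocation.
   - The T1 and T2 sections mention parents/carers only for condition 2, so on that wording a parent's presence can point to the arm.
   - The research team helps with monitoring procedures meant to support fidelity (Condition 1 section), which is likely to show its members where the intervention is delivered.

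5. **Which outcomes depend on these contacts?** In the outcome list, the TROM and the Personal Adjustment and Role Skills Scale are collected at T1 and T2 only. The measure used for sizing therefore has no baseline value and rests wholly on follow-up contacts.

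**Size.** The documents give no effect size, standard deviation or estimate of assessor bias, so the shift cannot be calculated. Sampling error can be put alongside it. Assume 50 young people spread evenly over 6 sites, 4 intervention and 2 control, giving about 33 against 17. Before dropout and clustering, the standard error of a standardised difference is √(1/33 + 1/17) = √(0.0303 + 0.0588) = √0.0891 ≈ 0.30 SD. A modest bias could not be told apart from noise in these data, so the results themselves would not reveal it.

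**The case against.** A reader might infer that the exempt roles are the ones most likely to make the follow-up visits, so that blinding covers hardly anyone who collects outcomes. The documents do not support that. They do not say who makes the visits, they give no staff numbers, and the blinding sentence presupposes other collectors who remain blind.

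Nor does the article conceal the position. It states that young people and health care staff are not blinded and exempts the other two roles in the next sentence. It makes no unqualified claim of blind assessment.

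Three further points limit the consequence, and all of them stand:
- The measures are described as questionnaires, with feedback sought from participants after completion, and no assessor rating is described. If participants complete them, the main source of bias is the unblinded respondent, which a blind visitor cannot remove.
- Not every contact need include an interview about the intervention. Only 30 such interviews are sought in all, parents/carers and staff are interviewed as random samples, and the listed T2 topics do not include the intervention.
- None of the progression criteria compares outcome scores between arms.

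It can also be said that task order is operational detail an article may leave to the full protocol. That is fair, and silence on order is not criticised in itself. What remains is a stated exemption that lets people who know the arm collect outcomes intended for an effect estimate and for sizing.

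**Conclusion.** The point holds in a limited form. As written, the plan allows unblinded people to collect T1 and T2 outcomes, and it identifies no administrator of those measures as blind. The added bias is limited, because respondents know their arm anyway, and its size cannot be given from the documents. The likely direction, towards the intervention, is an assumption.

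The conclusion rests on the literal reading of the exemption in Allocation Strategy and on the pairing of interviews with measures in the T1 and T2 sections. It does not depend on who actually makes the visits. If the full protocol already assigns the measures to blind collectors, only the article's wording needs attention. The change is worth making because it removes an avoidable source of bias at little cost, and because both the preliminary effect estimate and the TROM-based sizing draw on these data.

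**What to change.** At T1 and T2:
- Complete all questionnaires before any interview, by self-completion or with the follow-up collectors the plan already calls blind. Some participants have learning disabilities and may need help; that help should come from a blind collector.
- Use the principal researcher and fieldworkers for interviews only.
- Record any unblinding of a collector, with its timing relative to the questionnaires.
- State in the protocol which role administers the measures and whether that role is blind.

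Sending the exempt roles only to participants from sites where they did no other work would not serve, because they are exempt from blinding to the units' allocation as a whole.

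If no blind collector is available, say plainly that only the statistician is blind and that outcomes are participant-reported under open allocation.

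The cost is a fixed task order at an existing contact and a visit rota. Where the blind collectors already exist, or self-completion is used, no new staff are needed.
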